Government-approved policies and delivery modalities for screening and treatment	Process	Clinical and logistical guidance for providers' implementation of HOPE	Healthcare provider support and capacity building	Improved provider knowledge and self-efficacy in delivering HOPE. Pathway to sustained and structured HOPE implementation
Inter-agency collaboration in guiding and refining HOPE implementation	Relational tie	Social capital, sources of power involvement, existing infrastructure and resource alignment	Multiagency representation (e.g., SAB) for HOPE implementation	Synergy in government policy, existing resources and infrastructure for sustainable HOPE implementation at facilities
Government role in social network support for HOPE implementers	Relational tie Process	Implementation experiences Moral and technical support	WhatsApp^©^ group to foster social network support for providers implementing HOPE	Ongoing government, clinical (from Teaching Hospital) and peer support for providers implementing HOPE. Better insight into challenges and opportunities
Contribution of government/facility vs patient funding in HOPE intervention	Formal arrangement	Money	Discuss expectations and decision-making on funding arrangements for HOPE in SAB	Government and facility-level clarity, expectations set and concrete information shared on HOPE funding and degree of integration into routine care

Inner setting: health facility; Outer setting: government agencies, funding, policies, and procedures

Additional bridging factors may be identified, and ISS will be reviewed and refined during study implementation

At the end of the formative study, a ten-member Stakeholder Advisory Board (SAB) was convened among nominal group participants, comprising WLWH, healthcare providers, clinical managers, and policymakers. The Board provides high-level technical and contextual expertise in designing and implementing the intervention and in disseminating findings to the broader body of stakeholders in Ghana.

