#### Design

We will conduct a hybrid type 2 cluster randomized controlled trial to simultaneously evaluate the effectiveness and implementation of HOPE 2.0 using bridging factor-focused ISS. HIV clinics at the four selected secondary-level facilities will be cluster randomized 1:1 in a two-arm trial. WLWH in the intervention group will receive HOPE 2.0 from providers trained and supported to implement HOPE 2.0 using ISS-focused training materials and per the implementation plan developed in the Preparation Phase. After this intensive 6 month implementation phase, technical and clinical support from the study team and clinical experts to the intervention sites will be withdrawn, after which the Sustainment Phase will begin

WLWH in the control group will also receive HOPE, from providers without ISS or an implementation plan (Table 2 and Fig. 2). At the end of this 6 months period of implementation, the study team will provide ISS materials to control group health facilities to co-implement with HOPE 2.0. There will be a similar Sustainment Phase for the control sites.

**Table 2 Tab2:** HOPE-inG baseline provider training in intervention vs control arms

	**Topic**	**Intervention Arm**	**Control Arm**
1	Epidemiology of cervical cancer (CC) in women with and without HIV	Yes	Yes
2	The WHO cervical cancer elimination agenda	Yes	Yes
3	The HOPE intervention: components and evidence	Yes	Yes
4	Cervical cancer screening strategies	Yes	Yes
5	Pre- and post cervical screening counselling	Yes	Yes
6	Psycho-social support for clients with positive cervical screening results and their immediate family	Yes	Yes
7	Awareness creation, record keeping and documentation	Yes	Yes
8	Research ethics: participant recruitment, study procedures and collecting, documenting and reporting data	Yes	Yes
9	Delivering the HOPE intervention in Ghana: Implementation research to practice	Yes	No
10	Who is supposed to do what, where and when? The HOPE 2.0 implementation plan	Yes	No
11	How will we deliver the intervention? Implementation support strategies for HOPE 2.0	Yes	No
12	What resources do we have for successful implementation? Additional tools, job aids, support and training for delivering HOPE 2.0	Yes	No

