### Outcomes measures

The primary outcomes of interest in this type 2 hybrid trial are 1) the effectiveness of the HOPE 2.0 intervention in increasing uptake of cervical screening among WLWH, and 2) the adoption of HOPE 2.0 intervention at the facility level. Other outcomes, including cost, fidelity, penetration, and sustainability, will be assessed as secondary outcomes. Additionally, Proctor et al.’s [61] client (i.e., WLWH) health outcomes will also be assessed (Fig. 2).*Cervical screening uptake* is defined as the proportion of WLWH in each study arm that successfully complete the cervical screening process. In the intervention arm, completing the process requires the WLWH to present to the clinic, collect a self-test kit, collect a cervical sample, and submit the sample to the clinic for testing. In the control arm, completing the process requires the WLWH to present to the clinic and receive a pap smear/cervical sample collection from a provider. WLWH in either study arm who do not complete the entire process will not be considered as completing uptake. Uptake assessment will therefore be determined as proportion of WLWH with complete screening out of all women enrolled in each study arm.*Program Adoption* is defined as the decision of healthcare workers (i.e., providers and management) and patients (described as patient uptake) to commit to and use HOPE 2.0 and ISS adoption. Adoption will be measured at provider, management, and patient levels using a variety of data logs, surveys, and interviews.At the management level, we will assess (i) the number of ISS training sessions attended and (ii) the degree to which ISS components are used to support providers.At the provider level, we will assess (i) the number of ISS training sessions attended, (ii) the degree to which ISS components are used, and (iii) the number of implementation plan steps followed. Additionally, we will assess providers’ (i) implementation experience (i.e., resource availability, managerial support, and technical issues confronted); and (ii) operational experience (i.e., workload increase or decrease, flow of health facility communication, and any skills needed).*Implementation Cost* is defined as the total expenses (facility/provider and patient) for implementing HOPE 2.0. Cost will be assessed at the health facility level in both study arms. We will use a micro-costing approach to estimate the economic costs associated with each study arm. The direct measure method of micro-costing involves tracking resources used and enumerating unit costs for each resource to precisely estimate cumulative costs associated with each study arm [62]. Implementation cost will be measured at the health facility level and patient level, utilizing a variety of cost-tracking databases throughout the study period to itemize, quantify, and value resources.At the health facility level, a cost-tracking database will be used throughout the study period to itemize, quantify, and value resources. Costs at the facility level include (i) number of hours staff spent on HOPE 2.0 training; (ii) sampling materials, including kits and laboratory testing costs; (iii) recruitment (i.e., time spent identifying and contacting eligible women, advertising materials, participant incentives); (iv) HOPE 2.0 delivery (with and without ISS); and (v) treatment and biopsies.Cost to the patient will include tracking of participant out-of-pocket costs (e.g., transportation, childcare, phone data, time spent on HOPE 2.0 procedures). French et al.’s outpatient cost survey [63] (5 items) will be adapted to measure patient-level costs.Note: Time effort will be estimated using the hourly wages of WLWH and healthcare workers.*Fidelity* is the degree to which HOPE 2.0 and its ISS are implemented as planned.At the provider level, utilizing surveys, log sheets, and interviews, we will assess (i) the degree of adherence to HOPE 2.0/ISS protocols (Intervention) and HOPE 2.0 (Control) during implementation, (ii) the dose of the program delivered, and (iii) the quality of program delivery.At the management level, we will assess (i) adherence to ISS protocol (Intervention only) and (ii) overall management support for providers (both arms).We will utilize log sheets and interviews, as well as observations, and the Process Evaluation Checklist (PEC) [64] throughout to track the fidelity of implementation and overall project progress.*Program Penetration* for this proposal is the integration of HOPE 2.0/ISS within the HIV subsystem of study facility settings [61]. We will assess penetration outcomes at provider and management levels by determining the proportion of personnel who actually deliver on a HOPE 2.0 program task/role, out of the number trained or expected to deliver on that task/role.At the management level, we will utilize log sheets and interviews to measure the expected tasks or roles to be evaluated, which will be (i) the provision of technical support and (ii) facilitating a conducive HOPE 2.0 implementation climate for providers.At the provider level, we will utilize log sheets and interviews to measure the expected tasks to be evaluated, which are (i) screening and recruitment of eligible WLWH, (ii) delivery of HOPE 2.0 to enrolled WLWH, and (iii) follow-up on all testing outcomes and completion of required documentation for these tasks/roles.*Program Effectiveness* is defined as the impact of the ISS on 1) providers' self-efficacy in implementing HOPE 2.0, 2) WLWH screening uptake, and 3) treatment outcome. We will assess effectiveness outcomes at management, provider, and WLWH levels utilizing surveys, log sheets, and interviews.At the management level, we will assess (i) the frequency of support that management delivers to providers, (ii) management self-efficacy in supporting HOPE 2.0 implementation, and (iii) challenges in supporting HOPE 2.0 implementation at their facilities, utilizing log sheets and interviews.At the provider level, we will assess (i) self-efficacy for implementing HOPE, (ii) fidelity of HOPE 2.0 intervention delivery, (iii) number of WLWH screened and women with positive results who are treated, and (iv) the type, frequency, duration, and quality of service provided to patients (WLWH).At the WLWH level, we will assess the impact of HOPE 2.0 on patients’ (WLWH) screening uptake (i.e., service outcome) and receipt of screening results, patient satisfaction, and for women with positive screening results, clinical follow-up, and evaluation for, and receipt of CC treatment where appropriate (i.e., client outcomes). Assessment procedures: WLWH in both study arms will complete the screening and satisfaction outcome survey within one month of completing HOPE 2.0. Within one month of screening, providers will check the lab registry and will review the electronic medical record to confirm screening completion. Treatment compliance will be evaluated within 6 months of positive result notification. The screening and treatment completion outcomes will be binary (yes/no), test results (positive, negative, or inadequate), treatment follow-up (yes, no, or lost-to-follow-up), and patient satisfaction will be measured using a patient satisfaction survey [65].

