#### Quantitative data analysis

Descriptive analysis will be used for implementation outcomes scores at each health facility; scores will be compared within health facilities and between study arms over time. Mixed models (Linear Mixed Models or Generalized Linear Mixed Models) will account for repeated participant measures.*For Likert scale items (surveys)*, we will use ANOVA to determine differences in implementation outcome scores between study arms, with Tukey HSD (honestly significant difference) post hoc analysis to determine specific sites that significantly differ.*For continuous outcome variables*, we will similarly use linear mixed models to analyze treatment effects while controlling covariates, including age, education, income, religion, marital status, employment, insurance, and clinical conditions consistent with our previous studies [68, 69].*Fidelity analysis:* The fidelity checklist and activity log sheets at each study site will be aggregated, and composite site scores will be calculated and compared across intervention and control sites.*Cost-Effectiveness Analysis:* Costs will be determined using the cost trackers described. At the facility level, we will use the WHO Incremental Cost-Effectiveness Ratio (ICER) [70]. A formula to analyze the cost-effectiveness outcome, whose outcome of interest is screening and treatment. An ICER is calculated by dividing the difference in total costs (incremental cost) by the difference in the chosen measure of health outcome or effect (incremental effect) to provide a ratio of ‘extra cost per extra unit of health effect. We will determine the Total Cost [average fixed and variable costs (TC)] for screening and treatment in IG (Arm 1) and CG (Arm 2), and cervical cancer cases averted (incremental effect) for each Arm. Then ICER = Incremental cost/Incremental effect. An ICER of less than 1 indicates that the control group is cost-effective, an ICER greater than 1 suggests the intervention group is cost-effective, and an ICER equal to 1 indicates a similar cost for both arms. At the patient level, we will calculate the average cost per patient in both arms.

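### The cost definition has no place for ISS effort supplied from outside the facility, so the incremental cost of ISS is biased downward by an amount the protocol does not let us estimate

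*Protocol article*

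**What the plan says.** The Outcomes measures section sets the boundary of the cost outcome. Implementation cost "is defined as the total expenses (facility/provider and patient) for implementing HOPE 2.0", and "Implementation cost will be measured at the health facility level and patient level". Among the facility-level items are "number of hours staff spent on HOPE 2.0 training" and, as the only entry that names ISS, "iv) HOPE 2.0 delivery (with and without ISS". A note adds: "Time effort will be estimated using the hourly wages of WLWH and healthcare workers". The stated purpose is to estimate by micro-costing the economic costs of each arm. Cost is a secondary outcome in this section, although the abstract lists it among the primary ones.

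The Cost-Effectiveness Analysis paragraph under Quantitative data analysis takes costs from the trackers, computes the ICER at facility level, and describes its cost input as the total cost "for screening and treatment in IG (Arm 1) and CG (Arm 2"). The incremental effect is given as cervical cancer cases averted.

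Other sections say who supplies ISS. Under Implementation phase, Design, after six months "technical and clinical support from the study team and clinical experts to the intervention sites will be withdrawn", so this support is present while the arms are compared. Table 1 lists technical support from officials to clinic management. For the messaging group it lists "Ongoing government, clinical (from Teaching Hospital) and peer support for providers implementing HOPE". The Control arm section says that control sites receive no ISS and no training on the implementation plan.

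**The concern.** Both arms deliver HOPE, and ISS is the main designed difference between them. The protocol defines ISS as strategies that work through links between the clinic and the policy and funding system, so part of the effort comes by design from people who are not facility staff. A cost account that stops at the facility and the patient can miss that part.

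The missed input would sit in one arm only, so it would not cancel in the difference. The protocol intends its findings to inform national policy, and one ISS component is meant to give government and facilities clarity on funding. A funder reading the ICER would want to know what the support took, including the part that the study team and government provided during the trial.

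**Working it through.** **Step 1. Compare the cost boundary with the suppliers of ISS.** The plan states no cost, unit price or ICER, so there is no figure to reproduce and the check is of the text.

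| Element of the cost plan | What it reaches | Names an external ISS supplier? |
|---|---|---|
| Definition of implementation cost | Facility/provider and patient expenses | No |
| Measurement levels | Facility and patient | No |
| Training item | Hours spent by staff | No; trainers' time is not mentioned |
| Item (iv), delivery with and without ISS | Listed as a facility-level cost | No; covers facility-side ISS effort |
| Wage source | Women and healthcare workers | No; could stretch to outside clinicians |
| ICER | Facility level | No |

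| External ISS input | Where stated | Intervention arm | Control arm, during comparison |
|---|---|---|---|
| Study team | Implementation phase, Design | Yes, for six months | No |
| Clinical experts | Implementation phase, Design | Yes, for six months | No |
| Government officials advising management | Table 1 | Yes | No |
| Government and Teaching Hospital support to providers | Table 1 | Yes, ongoing | No |

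The gap is clearest for the study team and government officials. It is less certain for clinical experts and Teaching Hospital clinicians, because they might be counted as healthcare workers under the wage note.

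**Step 2. Direction.** Let X be the cost of external ISS effort in the intervention arm; in the control arm it is 0 during the comparison. Let ΔC be the true incremental cost. If X is left out:

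reported ΔC = ΔC − X

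Since X is positive, the reported incremental cost is too low.

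**Step 3. Relative size.** Let f = X / ΔC, with ΔC positive and the incremental effect ΔE positive and unchanged. Then:

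reported ICER = (1 − f) × ΔC / ΔE = (1 − f) × true ICER

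true ICER / reported ICER = 1 / (1 − f)

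| f (assumed) | Reported as a share of true | True / reported |
|---|---|---|
| 0 | 1.00 | 1.00 |
| 0.10 | 0.90 | 1.11 |
| 0.25 | 0.75 | 1.33 |
| 0.50 | 0.50 | 2.00 |
| 0.75 | 0.25 | 4.00 |

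The ratio does not depend on which effect measure is the denominator, so it applies to cases averted as the plan has it. Every value of f is an assumption; the documents support none in particular.

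**The case against.** The strongest reply is that ISS is already costed. Item (iv) names it, the list is introduced as what the costs include rather than as exhaustive, and the aim is the economic cost of each arm. Measurement at facility level could mean where resource use is recorded, whoever pays for it. Part of this stands: ISS effort by facility staff is counted, and a generous reading could bring in outside clinicians. It does not remove the gap, because the definition limits itself in its parenthesis to facility/provider and patient expenses, and the wage note gives no rate for study-team or government time.

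A reader might infer from the cost input for screening and treatment that the ICER drops ISS altogether. The documents do not support that: the same paragraph draws its costs from the trackers described, which contain item (iv), and the phrase matches the outcome it names.

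A facility-plus-patient perspective is a recognised choice. That is true, but the article does not declare it as a perspective, and it sits badly with the stated aim of costing each arm. Nor is this only a matter of a condensed article leaving out tracker templates: the article states a boundary, and that boundary excludes something.

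Not all external effort belongs in the account. The Stakeholder Advisory Board also advises on design and dissemination, which is development or research work. Because study-team support is withdrawn after six months, how much of it a health system would have to buy is unclear. Both points stand and shape the fix.

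**Conclusion.** The point holds in a limited form. As written, the cost definition leaves out ISS effort supplied from outside the facility. That effort goes to the intervention arm only during the comparison, so the incremental cost and the ICER are biased downward. The conclusion is firm for the study team and government officials and less certain for external clinical experts and the Teaching Hospital. It assumes that the definition is followed literally and that the true incremental cost and effect are positive.

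The size cannot be given. A reader might infer that most of the cost difference between arms is missing, or that ISS will look almost free. The documents do not support either. Other differences between arms fall within the listed items: staff hours for the four extra training topics in Table 2, kits, tests and treatment for any additional women screened, and facility-side ISS effort. Patient navigators, who are existing site personnel, also differ between arms. Nor can a sum per extra woman screened be derived: the plan's effect is cases averted, its 15% and 30% are sample-size assumptions for implementation outcomes such as adoption, and no prices are given.

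A reader might also object that recruitment time and incentives are counted while external ISS is not. Those costs arise in both arms and so at least partly cancel, and identifying and contacting eligible women is partly a delivery task, so this adds little.

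**What to change.** State the costing perspective in the Implementation Cost definition. Add one line to the existing cost tracker for ISS hours and materials supplied to each site by the study team, external clinical experts, the Teaching Hospital and government, with a named wage source for each group. Include that line in the intervention arm's cost for the ICER, or report the ICER with and without it so that readers can choose the perspective they need. Record development and research-only effort separately, including the advisory board's design and dissemination work, and keep it out of the ICER.

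The cost is one extra log, some judgement in separating support from research, and a less favourable ICER. The log should start now: the article places the trial at the beginning of the Implementation Phase, and hours not logged as they occur are hard to recover later.

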#### Recruitment

*Doctors, nurses, patient navigators, and clinic managers:* We will meet with Medical Directors of the selected health facilities to discuss the study and the recruitment of providers. We will recruit providers by email, phone, and face-to-face contact.*WLWH* will be recruited using E-tracker electronic records. Participating providers at each site will identify eligible women from their site-level sampling frame (400–600 per site for a total pool of ~ 3,900 WLWH) and contact them by phone to solicit participation. Verbal informed consent will be sought in English/applicable local language by research coordinators prior to trial initiation. Participant recruitment is ongoing and will be completed by March 2028.*Community members* will be recruited from study communities via community gatekeepers.Ghana Health Service and the Ministry of Health will facilitate the recruitment of government officials through written and verbal invitations and snowball recruitment.

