#### Sample size estimation

The sample size is calculated based on implementation outcomes of health system adoption, cost, fidelity, penetration, and sustainability.*For power calculation*, we used Power (1 − β) = 0.8 and α = 0.05 and did not assume equal cluster sizes. The coefficient of variation (CV) of cluster sizes is set to 0.2, allowing for a large variability between clusters. Methods from Donner et al. [59] implemented in R for cluster RCTs were used.*For binary outcomes**,* e.g., adoption, we assumed 15% adoption in the control group based on previous study [23]. Table 3 shows the sample size needed to detect increases in implementation outcomes (e.g., adoption) in the intervention arm from 15% to 25–50% with 80% power. We expect to achieve an increase of at least 15%, to 30% or more, for outcomes such as adoption.*For continuous outcomes* such as sustainability/sustainment, we used estimated variance = 1 (standardized), and variance within clusters = 0.95 (assuming a large proportion of individual WLWH variability). For average cluster sizes (sampling frame per facility) ranging from 400 to 600 WLWH, we have greater than 80% power to detect differences in mean scores between the intervention and control arms as small as 1.4. We aim to recruit at least 1,152 patients (288 per site × 4 sites, inclusive of 20% attrition for a minimum sample size of 240 per site) Thus, the sample size for the Intervention Arm is *n* = 576 and Control Arm is *n* = 576.

**Table 3 Tab3:** Power and sample size calculation

Intervention Numeric	Control Numeric	Minimum Sample Size Per Site
0.25	0.15	504
0.30	0.15	240
0.35	0.15	142
0.40	0.15	94
0.45	0.15	67
0.50	0.15	50

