### Study procedures

#### Intervention arm

Step 1. Providers, i.e., clinicians, patient navigators, and clinic management at intervention sites will receive a) ISS delivered through management support, capacity-building, and social network support, and b) baseline and refresher training on the HOPE implementation plan.Step 2. Clinicians will a) screen and recruit eligible WLWH, and b) implement HOPE 2.0 by delivering 3R messages via WhatsApp to enroll WLWH.Step 3: WLWH will receive a self-sampling kit from clinicians or patient navigators to collect samples.Step 4: WLWH with positive screening tests will follow up for treatment per the WHO screen, triage, and treat cascade (Fig. 4). Patient navigators will support participants to follow up.

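### Implementation cost counts participant incentives and recruitment advertising, and does not exclude trial-only recruitment effort, so facility cost per arm is overstated as a programme cost

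*Protocol article*

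**What the plan says.** In Outcomes measures, implementation cost "is defined as the total expenses (facility/provider and patient) for implementing HOPE 2.0". The facility-level list then includes "i) number of hours staff spent on HOPE 2.0 training" and "iii) recruitment (i.e., time spent identifying and contacting eligible women, advertising materials, participant incentives", alongside kits and laboratory tests, delivery of HOPE 2.0, and treatment and biopsies. These are to be logged in a cost-tracking database in both arms.

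Four other places bear on what these items contain:

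- **Recruitment:** providers take eligible women from the site list and "contact them by phone to solicit participation".
- **Intervention arm, Step 2:** "Clinicians will a) screen and recruit eligible WLWH, and b) implement HOPE 2.0". Recruiting and implementing are two separate acts here.
- **Outcomes measures, Program Penetration:** the tasks expected of providers include "i) screening and recruitment of eligible WLWH". Here recruiting is part of the programme.
- **Table 2, row 8**, given in both arms: "Research ethics: participant recruitment, study procedures and collecting, documenting and reporting data".

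The Cost-Effectiveness Analysis paragraph takes its costs from these trackers and forms an ICER from total cost per arm for screening and treatment. The enrolment target is the same at every site: "We aim to recruit at least 1,152 patients (288 per site × 4 sites", and so on.

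**The concern.** The outcome is defined as the expense of implementing the programme, but the list used to measure it includes expenses of running the trial. The Background and The HOPE intervention sections describe HOPE 2.0 as self-sampling, the 3R communication model, patient navigators and implementation support strategies (ISS). Payments to participants are not among these, so a clinic delivering HOPE 2.0 as described would not pay them. Advertising and calls made only to fill the trial sample would also fall away in routine use.

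The article says the findings will inform national policy. Table 1 foresees the advisory board discussing how government, facility and patient funding should be arranged. Those readers need the cost of the programme, and a total that includes research lines overstates it. The ICER numerator may carry the same lines.

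**Working it through.** **1. Which items are research and which are programme.** Setting the sections side by side:

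| Item in the cost list | What the article says elsewhere | Reading |
|---|---|---|
| Participant incentives | In no described component of HOPE 2.0 | Research |
| Advertising materials | Listed under recruitment; purpose not stated | Research where it serves only the trial |
| Time identifying and contacting women | Calls solicit participation; Step 2 separates recruiting from implementing; Penetration lists recruiting as a provider task | Mixed; needs a split |
| Staff training hours | Table 2 row 8 is a research topic within the baseline training; no topic is excluded from the hours | Row 8 enters only by inference |

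**2. The enrolment target.** 240 × 1.2 = 288 per site; 288 × 4 = 1,152; 288 × 2 = 576 per arm. This reproduces the plan's figures. The article gives no cost figure to reproduce.

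**3. Effect of incentives on absolute cost.** Let I be the incentive per enrolled woman (not stated). Each arm's total rises by 576 × I and the study total by 1,152 × I, so average facility cost per enrolled woman rises by I. The difference between arms changes by 576 × I − 576 × I = 0 if the same rate is paid to the same number of women.

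**4. When the difference between arms would move.** Contacts needed at a site = 288 / consent rate. The consent rates are assumptions:

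| Assumed consent | Contacts per site |
|---|---|
| 90% | 320 |
| 80% | 360 |
| 60% | 480 |
| 50% | 576 |

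If the four sites had these four rates, the possible two-against-two allocations give:

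- (480 + 576) − (320 + 360) = 376 contacts
- (360 + 576) − (320 + 480) = 136 contacts
- (320 + 576) − (360 + 480) = 56 contacts

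At an assumed 20 minutes per contact (divide by 3), the arms differ by about 125, 45 or 19 staff hours. With equal consent at all sites the difference is zero.

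**5. Are these rates feasible?** Recruitment gives 400–600 women per site. At 50% consent a 400-woman site yields 200 and cannot reach 288; 576 contacts need a site near the top of the range. The same sentence gives a pool of about 3,900, or 3,900 / 4 = 975 per site, which does not agree with 400–600. The target is 288 / 400 = 72%, 288 / 600 = 48% or 288 / 975 = 30% of the frame, so the recruitment burden is itself uncertain.

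**6. Possible effect on a cost ratio.** Using the 15% and 30% of the sample size section purely as illustrative screening rates, the extra women screened are 576 × (0.30 − 0.15) = 86.4. Each 1,000 cost units of recruitment imbalance would then move the cost per extra woman screened by 1,000 / 86.4 = 11.6 units. This holds only if recruitment enters the ICER. The plan's ICER names cancer cases averted as its effect, so this figure shows only the mechanism.

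**The case against.** The strongest reply is that most of the recruitment item is not research. The Penetration definition counts recruiting eligible women as a provider task, and any clinic offering self-sampling must find and contact women. This stands: contact time should be split, not removed wholesale. It does not rescue incentives, which are named outright and belong to no programme component.

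Second, the research-ethics hours are an inference. The cost item speaks of HOPE 2.0 training and no sentence says that row 8 is booked there. Row 8 is one of twelve topics and is given in both arms, so it largely cancels in the difference if attendance is similar. This stands too.

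Third, a reader might infer that the cost difference between arms is biased, and that ISS will look cheaper than it is. The documents do not support that. They give no consent rates, and equal incentives cancel. Only intervention providers receive ISS and implementation-plan training, so a difference in recruitment effort could partly be a real effect of ISS that costing ought to capture.

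Fourth, a research-versus-programme tag might be detail left to the full protocol, and an itemised database can be split later. This is partly fair. But the article does more than leave a detail out: it states a rule that puts incentives into the cost of implementing HOPE 2.0. An incentive line can be removed afterwards, whereas untagged staff hours are hard to divide in retrospect.

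**Conclusion.** The point holds for absolute cost. As written, facility cost per arm includes participant incentives and recruitment advertising and does not exclude trial-only solicitation, so it overstates the programme cost. The conclusion assumes that incentives are actually paid, and the amount cannot be computed from the documents. Whether the ICER numerator inherits the overstatement is unclear, because that paragraph draws on the same trackers but speaks of total cost for screening and treatment.

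Distortion of the difference between arms is conditional. It requires trial-driven recruitment effort to differ between sites, which a fixed target of 288 per site and two sites per arm make possible but which nothing in the documents establishes.

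Two further inferences are not supported. The average cost per patient is not shown to be affected: it is calculated at the patient level, where the listed costs are out-of-pocket expenses and time. Nor is the cost figure beyond repair, because the tracker is itemised. Outcomes measures makes cost a secondary outcome (the Abstract groups it with the primary ones); the comparisons of screening uptake and adoption are untouched.

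**What to change.** Add a field to the cost tracker that marks each line as programme or research, and add a sentence on its use to the Implementation Cost definition:

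- Exclude from base-case implementation cost and the ICER: participant incentives, advertising and solicitation done only for the trial, and any hours of research-ethics or study-procedures training.
- Keep identification of and outreach to eligible women as a programme cost, in line with the Penetration definition.
- Report the research lines separately or in a sensitivity analysis that adds them back.
- State in the Cost-Effectiveness Analysis paragraph whether programme recruitment cost is part of total cost for screening and treatment.

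The cost is one tracker field and a sentence in each of two places. The drawback is that some contact time needs a judged split between outreach and trial recruitment; the splitting rule should be written down and applied identically in both arms. Recruitment is described as ongoing, so the tag should be added soon, while hours can still be coded as they are logged.
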